### Participant timeline {13}

The participant timeline is shown in Fig. 2.

**Fig. 2 Fig2:**
[figure not shown]
Schedule of enrollment, interventions, and assessments (SPIRIT figure). LIPUS, low-intensity pulsed ultrasound; CT, computed tomography; US, ultrasonography; SaO_2_, arterial oxygen saturation; PSI, pneumonia severity index; CPIS, clinical pulmonary infection score

### Sample size {14}

Sample size and power calculation are based on the primary outcomes. All sample size calculations assume two-sided analysis with a power of 90% (1-*β* = 0.90) at a significant level of *α* = 0.05. The use of therapeutic LIPUS in viral pneumonia has not yet been reported. Based on the time span of this clinical trial and the number of patients expected to meet the inclusion criteria in our hospital, it is estimated that a total of 66 participants will be required (1:1:1 allocation ratio). We anticipate minimal missing data (< 5%) for the primary outcome (day 7 pulmonary inflammation on CT images) because participants were all inpatients and we have daily contact with them during the treatment phase. With a dropout rate of approximately 5%, a final sample size of 70 participants is required.

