**Methods:**

Sixty eligible participants with clinically confirmed viral pneumonia will be assigned to either (1) intervention group (LIPUS stimulus), (2) control group (null stimulus), or (3) self-control group (LIPUS stimulated areas versus non-stimulated areas). The primary outcome will be the difference in the extent of absorption and dissipation of lung inflammation on computed tomography. Secondary outcomes include changes in lung inflammation on ultrasonography images, pulmonary function, blood gas analysis, fingertip arterial oxygen saturation, serum inflammatory factor levels, the sputum excretion volume, time to the disappearance of pulmonary rales, pneumonia status score, and course of pneumonia. Adverse events will be recorded.

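### 90% power is presented as the basis of a sample size that the text says came from feasibility, with no effect size or SD; the abstract's total also disagrees

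*Protocol article*

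**What the plan says.** The Sample size section of the protocol article opens: "Sample size and power calculation are based on the primary outcomes". It continues: "All sample size calculations assume two-sided analysis with a power of 90" percent "at a significant level of *α* = 0.05". The next sentence reports that no earlier data exist: "The use of therapeutic LIPUS in viral pneumonia has not yet been reported". The number then follows from a practical consideration, "Based on the time span of this clinical trial and the number of patients expected to meet the inclusion criteria in our hospital", and on that footing "it is estimated that a total of 66 participants will be required (1:1:1 allocation ratio"). The section ends with the dropout allowance: "With a dropout rate of approximately 5%, a final sample size of 70 participants is required".

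The Methods paragraph of the abstract gives another total: "Sixty eligible participants with clinically confirmed viral pneumonia will be assigned".

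The Primary outcome section names two comparisons: LIPUS group against control group, and treated against untreated areas within the self-control group. The Primary objective concerns the first of these.

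**The concern.** A power statement ties together a significance level, a difference to detect, a measure of variability and a sample size. Here the significance level and the power are given, the difference and the variability are not, and the text attributes the sample size to recruitment time and expected admissions. A number fixed in that way has 90% power for some difference, but the plan does not say which one, or that it was chosen because it matters.

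The stake is how a negative result will be read. The Discussion fixes in advance that LIPUS is to be judged poor if the LIPUS group does not differ statistically from the control and self-control groups. Beside a claim of 90% power, that rule invites a reader to take non-significance as good evidence of no worthwhile effect. The design may not support that.

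The differing total in the abstract adds a smaller problem: a reader cannot tell from the article how many patients are to be randomised.

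**Working it through.** **Inputs.** Two-sided alpha 0.05, target power 90%, total 66 before dropout, dropout about 5% and final total 70 come from the Sample size section. The 1:1:1 allocation comes from Trial design. An independent-sample test between groups comes from Statistical methods. The total of sixty comes from the abstract. Difference and SD for the absorption rates: not given, so results are in SD units. I assume a t test on a continuous absorption rate.

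**Step 1: the plan's own figures.**
- Dropout: 66 / 0.95 = 69.5, which rounds up to 70. This reproduces, so 66 and 70 are the same plan before and after dropout. As a check, 70 × 0.95 = 66.5.
- The 66 itself cannot be reproduced, because two of its inputs are missing.
- Sixty fits neither figure: 60 / 0.95 = 63.2, and 60 × 0.95 = 57.

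**Step 2: detectable difference, LIPUS against control.** With n = 66 / 3 = 22 per arm, the normal approximation is d = (z₀.₉₇₅ + z₀.₉₀) × √(2/n) = (1.960 + 1.282) × √(2/22) = 0.98 SD. The noncentral t distribution (42 degrees of freedom, noncentrality d × √(n/2) = d × 3.317) gives:

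| Quantity at 22 per arm | Result |
|---|---|
| Difference with 90% power | 1.00 SD |
| Difference with 80% power | 0.86 SD |
| Power at 0.8 SD | 74% |
| Power at 0.6 SD | 49% |
| Power at 0.5 SD | 37% |

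**Step 3: sensitivity to the total.** The difference with 90% power is 1.05 SD at 20 per arm (the abstract's sixty) and 0.98 SD at 23 per arm (about 70 with no losses). The choice of total hardly changes the answer.

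**Step 4: numbers that 90% power would need (t test, before dropout).** For 0.8 SD, 34 per arm, or 102 over three arms. For 0.5 SD, 86 per arm, or 258 over three arms.

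**Step 5: within-patient comparison.** A paired t test with 22 pairs (21 degrees of freedom, noncentrality d × √22) has 90% power at 0.73 SD of the paired difference. This SD is that of the difference between two areas in one patient, so it is not on the same scale as the SD in step 2.

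**The case against.** The best defence is that a journal article condenses the full protocol, which may contain an effect size and an SD, and that a size set by feasibility is legitimate for a first trial of a treatment. Both points are fair. A feasibility-based size is no fault in itself. But the article does not merely leave out the derivation: it states one, and that derivation is recruitment time and admissions. An effect size elsewhere would not undo this account of where 66 came from.

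A reader might infer four stronger things that the document does not support.

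- *The trial is underpowered, or 1 SD is an unrealistically large effect.* No SD is given for either absorption rate, so 1 SD could be a small or a large number of percentage points.
- *There are three conflicting totals.* There are two: 66 and 70 are linked by the dropout step, and only the abstract's sixty is out of line.
- *70 is wrong because it does not divide by three.* A 24/23/23 split is an ordinary outcome of 1:1:1 allocation and has negligible effect on power.
- *Power must be worked out with alpha split over the two primary comparisons.* At 0.025 the detectable difference at 22 per arm would be 1.10 SD. But the document states no split, and its Discussion calls LIPUS effective only if it beats both the control and the self-control group. Requiring both does not call for a split.

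**Conclusion.** The point stands. The Sample size section offers 90% power as the basis of a number that, by its own account, came from feasibility; with no difference and no SD, the 90% is not established. What can be said is conditional: with 22 evaluable per arm, the LIPUS–control comparison reaches 90% power only if the true difference is about 1.00 SD. At 0.5 SD that test would miss a real effect about 63% of the time (100% − 37%).

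These figures assume a two-sided t test at 0.05, roughly normal absorption rates, equal arms and 66 evaluable patients. They do not show that the trial is too small. They show that the article gives no ground for reading a non-significant result as coming from a trial with 90% power, which matters because of the rule in the Discussion.

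The abstract's sixty is a separate, plain inconsistency with the Sample size section, and nothing else in the article resolves it.

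**What to change.** Replace the power statement in the Sample size section with wording such as:

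> The sample size was set by feasibility. With 22 evaluable participants per arm and two-sided alpha 0.05, the LIPUS–control comparison has 90% (80%) power for a standardized difference of 1.00 (0.86), 74% for 0.8 and 37% for 0.5. The within-patient comparison (22 pairs) has 90% power for 0.73 SD of the paired difference.

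Correct the abstract to 70 enrolled for 66 evaluable. Next to the decision rule in the Discussion, add that a non-significant result must be read against these detectable differences.

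The cost is wording and a less favourable stated power; enrolment and design stay as they are. If the sponsor treats the change as a protocol modification, the article's own section on amendments requires ethics approval first and then a report in the trial register.

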### Recruitment {15}

Participants will be recruited from the Lingang Campus of Shanghai Sixth People’s Hospital Affiliated to Shanghai Jiaotong University School of Medicine, and they are all inpatients who have undergone laboratory and imaging examinations to confirm the diagnosis of viral pneumonia. The doctors will contact with the patients and their families, and after obtaining the informed consent from the patients themselves or their family members, doctors will conduct screening according to the inclusion and exclusion criteria. Only those who meet all recruitment requirements and do not meet any exclusion criteria will participate in this study.

## Assignment of interventions: allocation

### Sequence generation {16a} and concealment mechanism {16b}

Participants will be randomized into three groups (LIPUS group; control group; self-control group) in a ratio of 1:1:1 using a computer-generated randomization sequence. Research assistants not involved in clinical care or outcome assessment will prepare sequentially numbered, opaque, sealed envelopes based on the randomization list and ensure the confidentiality and independence of the allocation data. When appropriate, the assistant will open envelopes and ensure the coordination of therapeutic interventions.

### Implementation {16c}

The sealed envelopes will be opened and reconcealed during the first LIPUS stage, before intervention by the staff responsible for randomization. The code will then be notified to the LIPUS experimenter.

## Assignment of interventions: blinding

### Who will be blinded {17a}

Both patients and clinic staffs (caregivers, outcome assessors, and statistical analysts, etc.) will remain blind to group allocation. Whether the intervention is LIPUS-treated or non-stimulated will not be revealed throughout the study.

The clinician ([name]) who performed LIPUS therapy was not blinded to the grouping results and the course of treatment. The clinicians, [name] and [name], have access to the final trial dataset.

### Procedure for unblinding if needed {17b}

Once the analysis of the primary and secondary outcomes is complete, the identity of the three groups will be revealed.

## Data collection and management

### Plans for assessment and collection of outcomes {18a}

The primary outcome data will be collected at the baseline and the termination of treatment; the secondary outcomes will be collected at pre-randomization, a fixed time every day and/or after 7 days of treatment. All variables in the protocol will be documented in an encrypted Microsoft Office Excel. The investigators who enter information into the office excel are responsible for ensuring the accuracy and completeness of information. A day-to-day management group, consisting of the principal investigator, a doctoral student, a research coordinator and an assistant manager, conducts clinical monitoring activities.

### Plans to promote participant retention and complete follow-up {18b}

The patients will complete all evaluations and treatments during hospitalization. Lung CT examinations, ultrasound examinations, and trial-related laboratory examinations received by patients before and after treatment are provided free of charge. Once a patient withdraws from the study during treatment (does not complete the full 7-day treatment period), their data will not be retained. Every effort should be made to encourage patients to remain in the study for the duration of their planned outcome assessments.

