### Criteria for discontinuing or modifying allocated interventions {11b}

Patients are free to withdraw from participation in the study at any time upon request, without any consequence. If a participant chooses to discontinue the study intervention, we will not collect or use their data.

LIPUS is an FDA-approved and safe treatment modality. To date, no adverse events have been reported with the low-power LIPUS regimen in soft tissue. Therefore, we anticipate that the risk to the safety of participants will be minimal. However, nursing staff will still monitor potential mild adverse reactions such as mild local swelling, spotting bleeding, enhanced local pain response, and local hyperesthesia or decrease. In case of corresponding symptoms, appropriate symptomatic treatment shall be carried out. Regardless, participants can withdraw from the study at any time if they experience adverse events that are unacceptable to them.

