## Outcomes {12}

### Primary outcome

The primary outcome measure will be the difference in the extent of absorption and dissipation of lung inflammation on CT images. Result comparisons will be made between the test group and the control group and between the LIPUS-treated and non-treated areas within the self-control group.

Pulmonary inflammation on CT images will be assessed by an expert chest radiologist before and 7 days after treatment to compare the area and volume of inflammation in the target area of the lung, as well as the area absorption rate (AAR) or volume absorption rate (VAR). A Pair software will be used to mark and 3D reconstruct the target area of CT images and record the data of pulmonary inflammation changes. AAR is defined as [(target site inflammation area before treatment − target site inflammation area after treatment)/target site inflammation area before treatment] × 100 (%). VAR is defined as [(target site inflammation volume before treatment − target site inflammation volume after treatment)/target site inflammation volume before treatment] × 100 (%).

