### Data management {19}

Investigators will collect data on participants’ baseline status and daily after randomization. All data obtained will be stored electronically in a securely accessible database and kept strictly confidential. The data transfer process will encrypt and any personally identifiable information will be deleted. De-identification of the data for analysis was allowed only during the final phase of this trial.

Registered participants will be withdrawn from the study if (1) the participant withdraws his/her consent and (2) the exclusion criteria is discovered after registration. The date and reason of the suspension will be recorded, and their data will not be retained.

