## Statistical methods

### Statistical methods for primary and secondary outcomes {20a}

Analysis of baseline characteristics of the three groups will be summarized by appropriate descriptive statistics. Analysis of both the primary and secondary outcomes will be performed blinded to treatment assignment and analyzed on the intention-to-treat approach [22], with all randomized participants retaining their original randomization group. If these missing data are judged to be random, multiple imputations of the chained equation will be used to address missing data caused by lost access and non-response.

Normally distributed data were expressed as the mean (standard deviation), whereas data not normally distributed was expressed as the median (interquartile range). The independent sample test was used for the comparison between groups, and the paired sample test was used for the comparison within the group before and after treatment. For clinical symptoms, variables were expressed as percentages. A *χ*^2^ test or Fisher’s exact test was used to compare categorical data. The conventional level of 0.05 for statistical significance was adopted to evaluate the *p*-values. Statistical analysis was carried out by using SPSS software, version 26.

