### Methods in analysis to handle protocol non-adherence and any statistical methods to handle missing data {20c}

We anticipate minimal missing data (< 5%) for the primary outcome (day 7 pulmonary inflammation on CT images) because participants were all inpatients and we have daily contact with them during the treatment phase. We will evaluate the impact of missing data by calculating the difference across plausible and extreme missing data scenarios. If our primary test is significant, we will also calculate the size of the interaction between the group and missingness required to make this difference non-significant. If 10% or more of the baseline samples are excluded due to missing data, we will use multiple imputation techniques for analysis.

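### Discarding the data of participants who stop early or are found ineligible contradicts the stated intention-to-treat analysis and can bias the LIPUS-versus-control comparison

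*Protocol article*

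**What the plan says.** Three places in the protocol article remove randomized participants from the data:

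- Criteria for discontinuing or modifying allocated interventions {11b}: "If a participant chooses to discontinue the study intervention, we will not collect or use their data". The same section names adverse events that a participant finds unacceptable as a reason to leave.
- Plans to promote participant retention and complete follow-up {18b}: "Once a patient withdraws from the study during treatment (does not complete the full 7-day treatment period), their data will not be retained".
- Data management {19}, for withdrawn consent or an exclusion criterion discovered after registration: "The date and reason of the suspension will be recorded, and their data will not be retained".

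The statistical sections say otherwise. Under {20a} the outcomes will be "analyzed on the intention-to-treat approach [22], with all randomized participants retaining their original randomization group". If missingness is judged random, "multiple imputations of the chained equation will be used to address missing data caused by lost access and non-response". Section {20c} adds "We will evaluate the impact of missing data by calculating the difference across plausible and extreme missing data scenarios", and then a size condition: "If 10% or more of the baseline samples are excluded due to missing data, we will use multiple imputation techniques for analysis". Sections {14} and {20c} expect less than 5% missing data for the primary outcome. Section {22} says that all adverse events are recorded.

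**The concern.** An intention-to-treat analysis needs the data of people who stop treatment. The three deletion sentences mean that those data are not collected, not used or not kept. The analysed set is then defined by events after randomization, and the comparison loses the protection of randomization to the extent that those events depend on arm and prognosis.

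This is not a detail that a separate analysis plan could settle. The rule governs collection and retention, and no later document can analyse records that were never made or were destroyed. The safety record is also affected: participants who leave because of an adverse event are the ones whose data matter most for harms.

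**Working it through.** **1. The rules side by side**

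| Randomized participant who | Deletion rule | What {20a} requires |
|---|---|---|
| stops only the intervention | {11b}: data neither collected nor used | analysed in assigned group |
| withdraws before finishing 7 days | {18b}: data not retained | analysed in assigned group |
| is found ineligible after registration | {19}: date and reason kept, data not | analysed in assigned group |
| withdraws consent | {19}: same | analysed, unless use of the data is refused |

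Reading {18b} as covering formal study withdrawal only does not remove the conflict, because {11b} still discards those who stop the intervention alone. No section limits deletion to people who ask for erasure.

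**2. Effect on the missing-data plan.** Imputation uses a participant's baseline and daily values to fill in a missing closing CT. For the rows above those values are gone, so neither the imputation in {20a} nor the scenarios in {20c} can include these participants. Both still work for a retained participant with a missed or unusable scan.

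**3. The plan's own figure.** 66 / (1 − 0.05) = 69.5, rounded up to 70, as stated in {14}. Under deletion about 70 × 0.95 = 66.5, say 66, are analysed. Under intention-to-treat all 70 are analysed, 3 or 4 of them with a missing closing CT. The required number does not change.

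**4. A yardstick.** The protocol gives no effect size or SD. With 66 / 3 = 22 per group, two-sided 5% and 90% power, the detectable difference is (1.960 + 1.282) × √(2/22) = 0.977 SD.

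**5. Size of the bias (assumed loss rates and mechanisms).** Suppose a share p of one arm is deleted from the poor end of a latent variable that has correlation ρ with the outcome, and there is no true effect. The bias in that arm's mean is ρ × φ(z_p) / (1 − p), where φ is the normal density and z_p the p-quantile. For p = 0.05: 0.103 / 0.95 = 0.109, so 0.05 SD at ρ = 0.5 and 0.10 SD at ρ = 0.9. Type I error comes from simulated t-tests (40,000 trials, 22 per arm, nominal 5%):

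| Deleted, arm 1 vs arm 2 | Bias (SD), ρ = 0.5 to 0.9 | Type I error |
|---|---|---|
| 5% vs 5%, or 20% vs 20% | about 0 | about 5% |
| 5% vs 0% | 0.05 to 0.10 | 5.3% to 6.0% |
| 10% vs 0% | 0.10 to 0.18 | 6.1% to 8.6% |
| 20% vs 5% | 0.12 to 0.22 | 6.5% to 11.2% |

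If deletion is unrelated to outcome (ρ = 0), bias is about 0 at every rate. At 5% versus 0%, the bias is about 5% to 10% of the 0.977 SD yardstick.

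**6. Upper-end cases.** If exactly the worst 2 of 22 (9%) are deleted from one arm and none from the other, bias is 0.17 SD and type I error about 10%. For the worst 4 of 22 (18%) the figures are 0.31 SD and about 19%.

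**The case against.** The case against a stronger reading is good, and most of it stands.

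- **Bias is possible, not shown.** A reader might infer that the rule does bias the primary comparison. The documents do not establish that loss depends on outcome or differs by arm. Sham wear and patient blinding work against differential loss, although {17a} says that the clinician giving LIPUS is not blinded. With equal loss under the same mechanism and no true effect, bias is about 0. In the self-control group both lung areas of a deleted patient go together, so selection between arms cannot arise there.
- **Expected loss is low.** The protocol anticipates under 5% missing, because participants are inpatients in daily contact. The 10% and 19% figures lie well beyond that.
- **Early discharge is not stated to be withdrawal.** The discharge criteria in the course-of-pneumonia section set no seven-day minimum, so a reader might infer that fast recoverers are deleted and the effect diluted. With a common recovery threshold that removes 10% of controls and is fully determined by absorption, a true 0.50 SD difference would appear as 0.32 SD. That same threshold removes about 22% of LIPUS patients (P(Z > 1.282 − 0.5) = 0.217), or about 39% if the true difference is 1.0 SD. No section supports such rates or says that a discharged patient has withdrawn, and {18b} expects treatment and evaluations to be completed in hospital. What remains is an ambiguity in the parenthesis of {18b}.
- **The two imputation conditions can be combined.** {20a} sets a condition on mechanism and {20c} one on amount. This is unclear rather than contradictory.

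None of these points reconciles the deletion sentences with intention-to-treat.

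**Conclusion.** The contradiction is explicit and must be resolved before analysis, because deletion cannot be undone. As written, the trial delivers a completers analysis labelled intention-to-treat and loses outcome and adverse event data on those who stop because of harm.

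The statistical consequence is a risk of unknown direction for the LIPUS-versus-control comparison. It is small at about the loss the protocol expects. It would be material only if loss were larger, related to outcome and lopsided, or if there were a true effect and outcome-driven loss. All bias and error figures rest on assumed loss rates and mechanisms, since the protocol gives none by arm or reason.

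**What to change.** Replace the deletion sentences in {11b}, {18b} and {19} with one rule. Stopping the intervention is not withdrawal from the study. Data already collected are kept, and planned assessments continue where the participant agrees. All randomized participants, including those found ineligible later, are analysed in their assigned arm unless a participant explicitly refuses use of their data.

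State in {18b} how a patient discharged before day 7 is classified for data purposes.

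Merge {20a} and {20c} into one missing-data rule: multiple imputation for any missing day-7 CT, no 10% trigger, and the {20c} scenarios as sensitivity analyses. Keep the fixed time point in the primary outcome section ("Pulmonary inflammation on CT images will be assessed by an expert chest radiologist before and 7 days after treatment") and treat a CT not obtained then as missing. Moving the closing scan to discharge would make outcome timing depend on recovery.

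Cost: amendment wording, a sentence in the consent form and a little more analysis work. The sample size does not change. A day-7 scan after discharge would need a return visit, so such scans may simply be missing and imputed.
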